## Abstract

**Background:**

Generalized anxiety disorder (GAD) is a highly prevalent and severely distressing condition that can lead to functional impairments and is considered one of the most difficult anxiety disorders to treat. Following new technological developments, a highly structured cognitive behavioral therapy (CBT) approach that has already shown success in face-to-face psychotherapy can be implemented: internet-delivered CBT (iCBT). There is now evidence for the efficacy of both guided and unguided iCBT interventions for GAD regarding symptom reduction.

**Objective:**

To establish the usefulness of such interventions, we plan to evaluate the efficacy of a web-based self-help program (Selfapy) for GAD in a relatively large sample. We aim to assess effects beyond symptom reduction, including effects on well-being, functioning, and mental health literacy, as well as the effect on health care burden, while testing the intervention in conditions comparable to routine care.

**Methods:**

Patients (n=156) who have been diagnosed with GAD, are aged between 18 and 65 years, have internet access, and have sufficient German language skills will be recruited for this study. The intervention group (n=78) will receive access to the 12-week self-help web-based program Selfapy. The waitlist control group (n=78) will receive no intervention in the context of the study. However, both groups will be allowed to access further health care services (eg, psychotherapy, medication), reflecting current routine care in Germany. Outcome measures will be assessed at baseline (T1) and 6 weeks (T2) and 12 weeks (T3) after the start of the intervention. The primary outcome will be generalized anxiety symptoms and quality of life at T3. Additional outcomes include depression, work capacity, therapy-related expenses and burdens, health literacy, and negative effects.

**Results:**

By May 2023, all participants had finished the trial and the report was being prepared for publication.

**Conclusions:**

Web-based interventions may be an important addition to the German health care system to reduce barriers to treatment access. Further, they may prove cost-effective for the treatment of GAD.

**Trial Registration:**

Deutsches Register Klinischer Studien DRKS00023799; https://tinyurl.com/22bds38x

**International Registered Report Identifier (IRRID):**

DERR1-10.2196/41440

## Introduction

### Background

Generalized anxiety disorder (GAD) is characterized by generalized and persistent excessive worry about various aspects of the past, present, or future without being confined to specific environmental conditions [1]. GAD can lead to severe distress and limitations in the daily lives of those affected [2] and is often associated with comorbid depressive disorders [3]. Subsequently, GAD poses an economic challenge to the health care system [4,5]. Lifetime prevalence is estimated at 6.2% [6].

GAD can be successfully treated by pharmacotherapy or psychotherapy [7]. Still, as individuals affected by GAD show lower response rates to therapies than other anxiety disorders, it is considered one of the most challenging anxiety disorders to treat [8]. One reason may be that individuals with GAD wait on average about a decade until they begin treatment [9]. Therefore, many cases remain undiagnosed and untreated, especially in the context of long waiting times and limited resources [9]. Following technological advancements, technology-based treatment alternatives have been increasingly developed over the past years to address the aforementioned problems [10]. Cognitive behavioral therapy (CBT) is especially suited for the transfer to web-based interventions due to its highly structured, directive, and standardized nature, as well as its emphasis on psychoeducation and homework [11]. In addition to being independent of limited resources, internet-delivered CBT (iCBT) also provides easier access for those who reject traditional forms of therapy due to stigma or other reasons [12].

Systematic reviews and meta-analyses [13] suggest that the use of iCBT programs for GAD compared to inactive control groups was significantly more effective and had moderate to large effect sizes (Hedges *g*=0.79) in reducing GAD symptoms. Further, iCBT programs for GAD achieved comparable effects to face-to-face CBT while the time required for each patient was 7.8 to 13 times less [14-17]. Of particular note is the benefit of iCBT to the health care system, as it may be a more cost-effective treatment alternative for GAD [18] since it can help reduce the waiting time for outpatient therapy, which averages 5 months in Germany [19] and has increased since the beginning of the COVID-19 pandemic [20].

While most of the literature focuses on guided forms of iCBT with therapeutic support, minimally guided, self-directed iCBT programs also show large effect sizes in the treatment of GAD (eg, Cohen *d*=2.43 [21]). Dear et al [22] found no significant differences between guided and unguided iCBT in terms of symptom reduction, completion rates, and satisfaction in the treatment of GAD. Moreover, first evidence suggests that characteristics of the guidance, such as the frequency of supportive monitoring [23], type of reminder (eg, phone, email), and the experience or training of the support person [24], do not have a significant influence on GAD symptom reduction. Nevertheless, it is important to take steps to promote adherence and minimize the typically high dropout rates of web-based, particularly self-directed, interventions [25] (eg, motivational content).

### Objective

Taken together, minimally guided web-based interventions provide a low-threshold method of access to mental health care and may be particularly helpful for GAD patients who often do not seek help [9]. We aim to establish further evidence for a web-based self-help program in a setting comparable to routine care. For this purpose, a comparison is made with a wait-list control group within a randomized controlled trial framework. Further, we want to address outcomes beyond symptom reduction, such as functioning in both daily life and the workplace, as well as mental health literacy and the health care burden.

## Methods

### Participants

Recruitment is carried out through newsletters and social media advertising drawing attention to Selfapy. Interested individuals can register for participation on the web, and after a successful video call–based screening procedure they will be contacted by the study center to schedule a diagnostic appointment.

Video calls will be conducted with all subjects, during which eligibility will be evaluated based on a diagnostic interview, the Diagnostic Interview for Mental Disorders–Open Access (DIPS-OA) [26]. Trained interviewers with at least a master’s degree (or equivalent) in psychology focusing on clinical psychology will conduct all interviews. The interviewers are trained at the Justus Liebig University in Giessen, Germany. Furthermore, there is close supervision on questions of diagnostics, as well as the inclusion and exclusion criteria, by a psychotherapist licensed in CBT.

Eligible subjects (1) are aged between 18 and 65 years, (2) have sufficient knowledge of the German language, (3) have uninterrupted internet access, (4) provide electronic informed consent to participate in the study, and (5) currently meet the diagnostic criteria according to the Diagnostic and Statistical Manual of Mental Disorders [1] for a diagnosis of GAD (International Classification of Diseases, 10th Revision code F41.1).

Subjects will be excluded if they do not fulfill any of the inclusion criteria or meet any of the following exclusion criteria: (1) past or current diagnosis of bipolar disorder, (2) past or current diagnosis of psychotic disorder, (3) current diagnosis of substance dependence, (4) current diagnosis of a severe major depressive episode, and (5) acute suicidality. A primary diagnosis of a disorder other than GAD is not an exclusion criterion, as we want to represent routine care. However, substance dependence, bipolar disorder, or psychotic illness are exclusion criteria because they conflict with the implementation of the program. Subjects who do not meet our inclusion criteria due to severity of illness are encouraged to seek professional help. Adequate language skills will be determined during the initial interview.

### Study Design

A 2-arm randomized controlled trial is being conducted to test the efficacy of the minimally guided web-based program Selfapy for GAD. The web-based course is defined as minimally guided as it is completed independently by the participant. However, as part of the patient safety concept, a psychologist monitors the participant’s progress to support the patient and respond to adverse events, such as suicidality. The participants can ask a psychologist questions about the program via an integrated messaging function. Figure 1 shows the schematic study design for patients in the intervention group and control group. After a structured diagnostic interview (DIPS-OA [26]) to clarify the inclusion and exclusion criteria, eligible patients will receive the first questionnaire and subsequently will be randomly assigned to the intervention group or control group. Patients in the intervention group will be able to use Selfapy immediately after randomization, while the control group will only have access to Selfapy after a waiting period of 12 weeks. Interim and final evaluations will occur 6 weeks (T2) and 12 weeks (T3) after the entry survey.

Subjects in the intervention group will have free access to the 12-week internet-based self-help treatment. Participants are advised to spend at least 15 to 20 minutes per day on the program. If no module is finished over 4 weeks, this will be counted as a dropout for an additional sensitivity analysis. Patients in the control group will not receive any treatment or support from the researchers during the first 12 weeks after the initial survey. However, they are free to seek any other assistance they desire, including pharmacological and psychological treatments. All concurrent therapies will be repeat-measured using self-reports.

**Figure 1 figure1:**
[figure not shown]
Flowchart of the study design for intervention and control groups. GAD: generalized anxiety disorder; CG: control group; IG: intervention group.

### Measures

Table 1 provides an overview of survey instruments at each time point, and more detailed descriptions are also provided below.

**Table 1 table1:** Survey instruments at each time point.

Time point	Survey instrument
Pretreatment measurement (T1)	Video interview: Diagnostic Interview in Mental Disorders–Open Access (DIPS-OA). Primary outcomes (self-assessed via web-based questionnaire) Generalized anxiety disorder symptomatology (Generalized Anxiety Disorder–7; GAD-7) Quality of life (World Health Organization–Five Well-Being Test; WHO-5) Secondary outcomes (self-assessed via web-based questionnaire) Coping with difficulties in everyday life due to illness (Work and Social Adjustment Scale; WSAS) Work Capability (Institute for Medical Technology Assessment Productivity Cost Questionnaire; iPCQ) Health Literacy (Mental Health Literacy Scale; MHLS). Reduction of therapy-related expenses and burdens for patients and their relatives (Client Sociodemographic and Service Receipt Inventory; CSSRI) Secondary outcomes Demographic questionnaire Anxiety symptomatology (Beck Anxiety Inventory; BAI) Depressive symptoms (Patient Health Questionnaire–9; PHQ-9)
Intermediate measurement 6 weeks after T1 (T2)	Same as T1, except that there is no video interview Further surveys Negative effects (Negative Effects Questionnaire; NEQ) Short demographic questionnaire
Posttreatment measurement 12 weeks after T1 (T3)	Same as T2

### Video Interview

The DIPS-OA [26] is used to classify mental disorders and record inclusion and exclusion criteria. The person conducting the interview is part of the evaluation team (ie, part of the Faculty of Psychology and Sport Science, Giessen University) and independent of Selfapy.

### Primary Outcomes

Generalized anxiety disorder symptoms will be assessed with the Generalized Anxiety Disorder Scale–7 (GAD-7 [27]). The GAD-7 consists of 7 statements rated on a 4-point scale and has an internal consistency of α=.92.

The measurement used to assess well-being is the World Health Organization–Five Well-Being Test (WHO-5 [28]). The WHO-5 consists of 5 items rated on a 6-point Likert scale and has an internal consistency of α=.92.

### Secondary Outcomes

Coping with functional impairments will be assessed with the Work and Social Adjustment Scale (WSAS [29,30]), which consists of 5 items for which the true score is given as a number between 0 and 8. The WSAS is used to assess the degree of functional impairment in various domains. The WSAS has been used in comparable studies, such as a study by Gräfe et al [31]. The internal consistency of the WSAS ranges from α=.70 to α=.94 [30].

Work ability and productivity are assessed via the Institute for Medical Technology Assessment Productivity Cost Questionnaire (iPCQ [32]). The iPCQ asks about long-term (>2 weeks) and short-term (<2 weeks) absences from work. In addition, the iPCQ includes three questions on productivity losses as a result of illness-related work efficiency limitations. The iPCQ was validated by Friedli et al [33].

The Mental Health Literacy Scale (MHLS [34]) will be used to measure mental health literacy. The MHLS consists of 20 items, of which the first 15 items are rated on a 4-point Likert scale and the remaining items are rated on a 5-point Likert scale. The internal consistency of the overall scale is α=.87. The MHLS has previously only been validated in English and was translated into German for this study with the involvement of a natively bilingual collaborator in a translation-backtranslation process.

Therapy-related expenses and burdens for patients and their relatives are captured using the Client Sociodemographic and Services Receipt Interview (CSSRI [35]). The CSSRI asks participants to report the actual service utilization (eg, contact with health care providers, number of therapy sessions, amount of contact with psychotherapists and psychiatrists).

### Additional Outcomes

The Penn State Worry Questionnaire (PSWQ [36]) is used to assess worry as an accompanying syndrome of GAD; it consists of 16 items rated on a 5-point Likert scale. The PSWQ shows internal consistencies approximately in the range between α=.84 [37] and α=.86 [38] in GAD patients.

The Beck Anxiety Inventory (BAI [39]) is used to assess the severity of anxiety in adults and adolescents. It consists of 21 descriptive statements rated on a 4-point scale. The internal consistency of the BAI is α=.90 in clinical samples. The German version was validated by Margraf and Ehlers [40].

The Patient Health Questionnaire-9 (PHQ-9 [41]) is used to assess the presence and severity of depressive disorders. The PHQ-9 consists of 9 items rated on a 4-point Likert scale and has an internal consistency of α=.89.

To capture possible negative effects of the intervention, the Negative Effects Questionnaire (NEQ [42]) is used, which consists of 32 items rated on a 4-point Likert scale. The NEQ has an internal consistency of α=.95.

The adherence of the intervention group is recorded via the log files of the web-based platform Selfapy. The number of modules that have been worked on is recorded.

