### Hypotheses

The main objective of this trial is to determine the efficacy of the 12-week Selfapy course for patients with GAD compared to a wait-list control group. Additional outcome data will be collected at 6 weeks. However, our confirmatory hypotheses, which will evaluate a positive health care effect, will focus on the 12-week outcomes. The following 2 hypotheses refer to our primary outcomes:

GAD symptomatology (measured with the GAD-7 [27]) will significantly decrease with the use of the Selfapy course for GAD after 12 weeks compared to a wait-list control group.Perceived quality of life (measured with the WHO-5 [28]) will significantly increase after 12 weeks of the Selfapy course for GAD compared to a wait-list control group.

The following secondary outcomes will only be analyzed if the hypotheses for the primary outcomes are confirmed. They will also be tested using Bonferroni-Holm adjustment:

Difficulties in daily life (measured with the WSAS [30]) will significantly decrease after using the Selfapy course for GAD after 12 weeks compared to a wait-list control group.Using the Selfapy course for GAD will lead to significantly better recovery of working ability (measured with the iPCQ [32]) after 12 weeks compared to a wait-list control group.Health literacy (measured with the MHLS [34]) will significantly improve with the use of the Selfapy course for GAD after 12 weeks compared to a wait-list control group.The extent of therapy-related efforts and burdens of patients and their relatives (measured with the CSSRI [35]) will be significantly reduced after using the Selfapy course for GAD compared to a wait-list control group after 12 weeks.

Our exploratory hypotheses do not address the target symptoms and are therefore not adjusted for α accumulation:

Worry symptoms (measured with the PSWQ [36]) will significantly decrease with the use of the Selfapy course for GAD after 12 weeks compared to a wait-list control group.Self-rated anxiety symptoms (measured with the BAI [39]) will significantly decrease with the use of the Selfapy course for GAD after 12 weeks compared to a wait-list control group.Self-rated depressive symptoms (measured with the PHQ-9 [41]) will significantly decrease with the use of the Selfapy course for GAD after 12 weeks compared to a wait-list control group.The Selfapy course for GAD will not lead to any side effects compared to a wait-list control group after 12 weeks (measured with the NEQ [42]).

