### Ethical Considerations

Participants are asked about suicidality at all measurement time points (T1, T2, and T3). For safety reasons, subjects will be contacted if they report suicidal thoughts and an emergency plan is drawn up with them. Nevertheless, the subject’s data will not be passed on to the police or other authorities. If participants endorse suicidality, they will be excluded from further data analyses, and only the assessments up to the occurrence of suicidality will be used.

The study center at the University of Giessen is responsible for storing and analyzing patient data. Besides the initial interview, all data are collected via a web-based platform (SoSci Survey; SoSci Survey GmbH) that uses SSL encoding to protect the data and stores them on servers located in Germany. Participant data are stored pseudonymously in order to access contact data in cases of suicidality. However, after the study is finished, the data will be immediately deidentified. Written informed consent is obtained from all participants before participation, and the ethics committee of the Faculty of Behavioral and Empirical Cultural Science at the study center at Heidelberg University approved the clinical protocol (AZ [name] 2021 1/1). The trial is registered at the German Clinical Trials Register (DRKS00023800) and follows the ethical principles of the Declaration of Helsinki. All patients receive an allowance of €30 (US $33) after completing the study.

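### The only stated between-arm side-effect comparison rests on the NEQ, on which the two arms may be rating different exposures, while harm data collected alike in both arms get no harm analysis

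*Protocol article*

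**What the plan says.** **The instrument and its purpose.** Under Additional Outcomes the protocol article states: "To capture possible negative effects of the intervention, the Negative Effects Questionnaire (NEQ [42]) is used". It gives the scale as 32 items on a 4-point format. Table 1 places the NEQ at T2 and T3, with no baseline value and no split by arm.

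**The comparison.** The last exploratory hypothesis under Hypotheses is that the Selfapy course "will not lead to any side effects compared to a wait-list control group after 12 weeks", with the NEQ as its only measure. On the group of hypotheses to which it belongs, the article says: "Our exploratory hypotheses do not address the target symptoms and are therefore not adjusted for α accumulation".

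**What controls are exposed to.** The abstract says: "The waitlist control group (n=78) will receive no intervention in the context of the study". Study Design adds: "Patients in the control group will not receive any treatment or support from the researchers during the first 12 weeks after the initial survey". It continues: "However, they are free to seek any other assistance they desire, including pharmacological and psychological treatments". According to the abstract, use of other health care is open to both groups.

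**Other data that bear on harm.** Table 1 lists GAD-7 and PHQ-9 at T1, T2 and T3. Ethical Considerations has suicidality asked at the same three time points. The Hypotheses section uses GAD-7 and PHQ-9 only for improvement. Statistical Analyses adds response rates and service use. Suicidality leads to contact with the participant and to removal of that person's later assessments from the analyses. No between-arm comparison of worsening or of suicidality is stated.

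**The concern.** A randomised contrast is interpretable when the outcome has the same meaning in both arms. On the stated purpose, an NEQ score refers to negative effects of an intervention. Before T3 an intervention patient has Selfapy to rate. A control may have outside psychotherapy or medication to rate, may rate the wait, or may have nothing to rate.

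If so, the contrast can mislead in either direction. Near-empty control scores would make ordinary reports about Selfapy look like excess harm. Controls who rate another treatment could hide a real excess. With no T1 value, the NEQ cannot be read as change from baseline either.

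What is at stake is the report's statement on side effects. Data with the same meaning in both arms are already in hand and would address that question more directly, but the article gives them no harm role.

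**Working it through.** **1. Sample size to work with.** The article states no figure for the NEQ comparison. Its general figure is 78 per group, from d = 0.45, a directed test at 0.025 and power 0.80. Check: n = 2 × (1.96 + 0.84)² / 0.45² = 2 × 7.84 / 0.2025 = 77.4, so 78 per arm and 156 in total. The figure reproduces and this point does not affect it. It is used below with no allowance for dropout.

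**2. Exposure that each arm could rate before T3.**

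| | Intervention arm | Control arm |
|---|---|---|
| Selfapy | yes | no |
| Outside therapy or medication | possible | possible |
| Nothing except the wait | no | possible |

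The share of patients in outside care is not given for either arm. It could be anywhere from 0 to 100%, so the mix of exposures behind the control scores is unknown.

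**3. What a difference in exposure alone could produce.** As an assumed extreme, let controls report no NEQ effect because they have nothing to rate, and let a proportion p of the intervention arm report at least one. With a two-sided 0.05 test, 78 per arm and p̄ = p/2, the normal approximation is

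power = Φ{ [p − 1.96 √(2 p̄(1 − p̄)/78)] / √(p(1 − p)/78) }.

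For p = 0.10: [0.10 − 1.96 √(2 × 0.05 × 0.95/78)] / √(0.10 × 0.90/78) = (0.10 − 0.0684)/0.0340 = 0.93, so power is 0.82. The same formula gives 0.52 at p = 0.05 and 0.99 at p = 0.20. A significant result would then be likely even if the control zeros reflected only the lack of a treatment to rate. These rates are assumptions, and the case is a bound, not a forecast.

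**4. What the symmetric measures could offer.** Reliable worsening is a change larger than 1.96 × √2 × √(1 − α) in SD units, taking the article's internal consistency as the reliability:

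- GAD-7, α = .92: 1.96 × 1.414 × √0.08 = 0.78 SD.
- PHQ-9, α = .89: 1.96 × 1.414 × √0.11 = 0.92 SD.

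The article gives no SDs, so these thresholds cannot be turned into scale points here.

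The 95% half-width for a risk difference at equal rates p is 1.96 √(2p(1 − p)/78):

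| Assumed rate per arm | Half-width, percentage points |
|---|---|
| 5% | 6.8 |
| 10% | 9.4 |
| 15% | 11.2 |

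Against a control rate of 5%, about 20% in the intervention arm would be needed for 80% power (two-sided 0.05). These comparisons are suited to estimation, not to a verdict by significance.

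**5. Effect of the exclusion rule.** A participant who endorses suicidality at T2 has no usable T3 assessment under Ethical Considerations, and so drops out of any T1-to-T3 worsening count. At 5% the expected count is 0.05 × 78 = 3.9 per arm, and each patient is worth 1/78 = 1.3 points. Losing one or two such patients would matter, and they are among the most informative about harm.

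**The case against.** The strongest reply is that the instrument is not shown. The stated purpose tells us why the NEQ was chosen, not how its items are worded. If they record unwanted experiences over a period without tying them to a treatment, controls supply the background rate that a randomised comparison needs. An adapted control version may also exist. This stands, and it is why the point is conditional.

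Second, outside care is open to both arms, and the Discussion frames the aim as the increment over current German care. Under that aim, negative effects of all care received could be a coherent contrast. This also stands in part, but the article defines the outcome as negative effects of the intervention, not of all care.

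Third, GAD-7 and PHQ-9 means are compared between arms, so worsening on average would show, and suicidality is asked about and acted on. That is correct. What is missing is any stated comparison of how many patients worsen or endorse suicidality.

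Fourth, an unseen analysis plan may contain such tables. It may. But the article itself fixes instrument, comparator and time point for its side-effect hypothesis, so the pairing is a stated choice and not a gap left to another document.

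A reader might go further and infer that the NEQ contrast is meaningless and must be dropped, or that the trial ignores its harm data. The documents do not support either. The first would need the item wording. The second overlooks the efficacy comparisons and the participant-safety use of the suicidality question.

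**Conclusion.** The point holds in conditional form. As described, the NEQ contrast may compare ratings of different exposures, so a difference or its absence cannot, by itself, be attributed to Selfapy. That conclusion rests on the purpose stated under Additional Outcomes and would fall away if the items prove free of attribution to a treatment and are given identically in both arms.

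The size of any distortion cannot be computed from the article. The 0.82 probability above belongs to an assumed extreme: 10% reporting in one arm, none in the other. The proposed comparisons have an unambiguous meaning but limited precision, about ±7 points at an assumed 5% rate.

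The hypothesis is exploratory, and neither the sample size nor any primary or secondary conclusion depends on it. The change is worth making because it is cheap and lets the trial address its own side-effect question.

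**What to change.** - **NEQ.** Report it descriptively in the intervention arm, as effects attributed to Selfapy. Show control-arm scores only with the caveat that the exposure rated may differ, and state how controls were asked to complete it.
- **Between-arm harm comparison (exploratory).** Use the proportion with reliable worsening on GAD-7 from T1 to T3, the same proportion for PHQ-9, and the proportion endorsing suicidality in the T2 or T3 questionnaires. Give each as a risk difference with a 95% confidence interval.
- **Suicidality source.** Count only questionnaire answers, because psychologist monitoring and messaging within the course exist only in the intervention arm.
- **Exclusion rule.** For this analysis alone, exempt participants from the rule that removes assessments after suicidality is endorsed, so that they stay in numerator and denominator. If their later assessments do not exist, say so and give the number per arm.
- **Labelling.** Participants have finished and the results paper was in preparation, so mark these analyses as added later unless the analysis plan already has them.

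**Cost.** One hypothesis reworded and a few extra tables, with no new data collection. The estimates will be imprecise, and the NEQ contrast will carry less weight.
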